## Abstract

**Background:**

Recent population-based surveys have reported that large majorities of children in France, Europe and in the US are not complying with international physical activity (PA) guidelines. There is, therefore, a need to find programs that will improve children’s PA habits from an early age. Theory-based interventions that include school, family, and community involvement have the potential to generate a considerable increase in the PA level of children. The theory of planned behavior (TPB) is one of the most widely tested models of the factors influencing health-related behaviors. The Great Live and Move Challenge (GLMC) is an extended TPB-based intervention designed to promote PA in French primary school children aged 7–11 years. The objective of this paper is to describe the protocol of a randomized controlled trial to evaluate the effectiveness of the GLMC on the PA level of children.

**Methods:**

This is a two-year cluster-randomized controlled trial comparing an intervention group to a control group, randomized into clusters (community of communes) and stratified by department (Hérault, Gard, Aude) and residential environment (urban, rural). The goal is to recruit 4000 children. The GLMC involves children and their parents, and multiple local grassroots partners, such as school teachers, municipal officials and policy stakeholders. The intervention will be delivered over 3.5 months per year for a two-year period. Pre- and post-intervention, children and parents will be asked to fulfill a questionnaire concerning current PA level, TPB variables (i.e.*,* intentions, attitudes, subjective norms, perceived behavioral control) and other psychosocial variables (e.g.*,* perceptions of activity opportunities). A subsample of 400 children will be proposed to wear an accelerometer (i.e.*,* the Actigraph GT3X+). The primary hypothesis is that the GLMC intervention will increase the proportion of children achieving the World Health Organization’s recommended 60 min of moderate to vigorous PA per day by 15%.

**Discussion:**

This study will evaluate the effectiveness of a multilevel, theory-based PA program and potentially provide valuable information for schools and public health officers looking for innovative PA programs.

**Trial registration:**

ISRCTN:61116221, 19/06/2018.

## Background

There is ample evidence that being physically active is a key protecting factor against non-communicable diseases that develop over the lifespan (e.g., coronary heart disease, cancer) [1–3]. International guidelines recommend a minimum of 60 min of moderate to vigorous physical activity (PA) per day for children [4, 5], but recent population-based surveys have reported globally insufficient PA levels in young people: more than 80% of US adolescents [6], 66% of European adolescents [4], and 69% of school-aged children in France were not complying with international guidelines [7]. Childhood (i.e., 4–12 years old) is considered a critical period for the formation of PA habits [8], notably in the perspective of preventing PA decrease reported during the adolescence (i.e., 12–19 years old) [9, 10]. Hence the promotion of PA in school-aged children is a public health priority of the World Health Organization [11].

Recent meta-analyses of controlled trials of interventions intended to promote PA in children have revealed that they produce significant increases in PA level, but the effects are small [12] (Cohen’s *d* was 0.07 in children less than 10 years old) and the quality of the evidence is limited [12, 13]. Finding out how to enhance the effectiveness of PA programs in children is therefore a big challenge. Recent evidence suggests that multilevel interventions involving school, family and community are the best way of increasing PA [14]. Involving schools has the advantage that all children, including those from the most socioeconomically deprived communities, are exposed to the intervention. In addition, involving parents is important in promoting parental commitment to ensuring children undertake regular PA. Thus the involvement of public policy stakeholders appears essential to influencing the physical environment in which children and their family live [14–16].

Most of previous interventions have suffered from failure to understand the psychosocial mechanisms underlying behavioral change [17–19]. Implementing interventions based on a psychosocial theory is one way to identify the principle psychosocial variables related to target behaviors, thus enabling the selection of relevant intervention techniques [20]. The theory of planned behavior (TPB) [21] is one of the most widely tested models of the factors influencing health-related behaviors [22] and has been shown to be particularly suited to prediction of PA [23].

The Great Live & Move Challenge (GLMC) is a multilevel, extended TPB-based program which aims to promote PA amongst school-aged children (7–11 years old). This paper describes the protocol of a cluster-randomized controlled trial evaluating the effectiveness of the GLMC. Three factors make the GLMC study an original contribution to research on promotion of PA in children: (i) the use of a theory-based approach that follows current recommendations about linking behavioral change techniques to the theoretically derived target variables [24], (ii) the integration of 3 levels of PA promotion (i.e., school, family, and community) and (iii) the inclusion of an objective method of measuring of the impact of the intervention on PA (i.e., accelerometers), which remains rare in studies of children [12].

## Methods/design

The protocol was approved by the French Advisory Committee on Information-Processing in Material Research in the Field of Health (Comité Consultatif sur le Traitement de l’Information en matière de Recherche dans le domaine de la Santé, CCTIRS) (registration no. 15279) and the French Data Protection Authority (Commission Nationale de l’Informatique et des Libertés, CNIL) (registration no. 1860542). Any modifications to the protocol will be agreed by the sponsor (INCa) and ethic committee prior to implementation and notified to the health authorities in accordance with local regulations.

### Study objectives

The primary objective of this study is to measure the effects of the multilevel extended TPB-based GLMC intervention on PA; the intervention is intended to increase by 15% the proportion of children meeting the current international recommendation of 60 min of moderate to vigorous PA per day at 24-month follow-up (i.e.*,* T3-post-intervention 2; see Fig. 1)*.*

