### Study design and population

All the year 3 and year 4 children attending primary schools in the Hérault, Gard, and Aude departments of France (and their parents) are eligible to participate in the study. There is wide variation in the sociodemographic background and PA levels of children attending schools in these departments. The intervention involves children and their parents, and is implemented by multiple local, grass-roots partners, namely, school teachers, municipal officials and policy stakeholders from community agencies and district councils. To avoid contamination between the intervention and control groups randomization will be done at community of communes level (a community of communes is an administrative grouping of several cities or villages), thus all the schools in a given community of communes will represent a cluster.

The study is a two-armed prospective cluster-randomized, controlled intervention trial. Communities of communes will be randomized in equal proportions to one of the two study arms: 1) the GLMC experimental arm, which will receive a 24-month (6 weeks per year) multilevel, extended TPB-based program intended to promote PA; 2) the control arm, which will not receive any intervention (Fig. 1).

After randomization, schools belonging to the communities of communes and their teachers will be informed about the study and their arm allocation by a research assistant. A member of staff outside the research team will introduce data into the computer in separate datasheets so that the researchers can analyze data without having access to information about the allocation. Eligible children from schools and classes willing to participate in the study, and their parents, will receive a written note explaining the research goal, design, assessment protocol (including information about the wearing of accelerometers) and intervention content (see flow diagram of schedule in Fig. 2). Children with medical conditions or and children taking medication that would limit their physical activity will not be included. Children will be given consent forms to take home for their parents to sign. There are three independent consent forms providing: *(i)* consent to the child filling in questionnaires; *(ii)* consent to fill in the parental questionnaires; *(iii)* consent to the child wearing an accelerometer.

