Module 6: Let’s make PA goals and plans!^a^	4 sessions	• Action planning • Goal setting	• Planning • Intentions	[75]	M6 Session 1 (Week 3 – duration: 15 min) • *Planning:* Each child plan the number of ‘energy cubes’ he/she will try to cumulate during the coming week in different areas of life (i.e.*,* recesses, lunch times) • *Goal setting*: Each child set a goal of total ‘energy cubes’ to cumulate during the coming week. M6 Session 2 (Week 4 – duration: 15 min) • *Planning:* cf. M6 Session 1 • *Goal setting*: cf. M6 Session 1 M6 Session 3 (Week 5 – duration: 15 min) • *Planning:* cf. M6 Session 1 • *Goal setting*: cf. M6 Session 1 M6 Session 4 (Week 6 – duration: 15 min) • *Planning:* cf. M6 Session 1 • *Goal setting*: cf. M6 Session 1	• Teachers
Module 7: Let’s practice PA altogether! ^a,b^	8 sessions	Implementation of PA sessions^c^	Perceptions of activity opportunities	[46]	M7 Sessions 1 & 2 (Week 3 – duration: variable, depending on “PA events”) • *Session 1, a “PA event” in the schools:* Teachers of each school organize a “PA event” for children during school hours (e.g.*,* Olympiad, treasure hunt, team based sport activities). • *Session 2, a “PA event” in the city:* Local policy stakeholders organize a “PA event” designed for families during the week-end in one quarter of the city (e.g.*,* family hike, giant Zumba lesson). M7 Sessions 3 & 4 (Week 4 – duration: variable in function of the ‘PA events’) • *Session 3, a “PA event” in the schools:* cf. M7 Session 1. • *Session 4, a “PA event” in the city:* cf. M7 session 2. M7 Sessions 5 & 6 (Week 5 – duration: variable in function of the ‘PA events’) • *Session 5, a “PA event” in the schools:* cf. M7 Session 1. • *Session 6, a “PA event” in the city:* cf. M7 session 2. M7 Sessions 7 & 8 (Week 6 – duration: variable in function of the ‘PA events’) • *Session 7, a “PA event” in the schools:* cf. M7 Session 1. • *Session 8, a “PA event” in the city:* cf. M7 session 2.	• Teachers • Municipal officials • Local policy stakeholders

*Note*. *BCT* behavior change technique, *GLMC* great live and move challenge, *PA* physical activity, *TPB* theory of planned behavior, *M* Module

^a^session indented for children; ^b^ session indented for parents; ^c^ such a behavior change technique is not referenced in the taxonomy of Michie and collaborators [45]

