### Evaluation

All variables will be measured at four time points (Fig. 1) i.e.*,* pre- and post-intervention in each year of the two-year intervention:year 1: pre-intervention 1 (T0); baseline;year 1: post-intervention 1 (T1); at the end of intervention 1, 4.5 months after baseline;year 2: pre-intervention 2 (T2);12 months after baseline, 7.5 months after the end of intervention 1;year 2: post-intervention 2 (T3); end of intervention 2, 16.5 months after baseline.

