#### Evaluation of children

##### Self-reported PA

PA is measured using an adapted version of the self-administered Physical Activity Questionnaire for Children (PAQ-C) [48] which covers PA undertaken in *(i)* sporting clubs or associations, *(ii)* break times at school, *(iii)* lunch times, *(iv)* free time and *(v)* as part of daily life. Children are asked to report the specific names of activities in which they have engaged together with the frequency and duration of each activity over the last 7 days. Total PA and PA in each domain are then calculated in hours per week. The validity and reliability of the PAQ-C have been demonstrated [49].

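### The primary objective is set at 24 months, but its measurement, T3, is scheduled at 16.5 months, at the end of the second intervention, and nothing is measured later

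*Protocol article*

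**What the plan says.** Under Study objectives, the primary aim concerns the proportion of children "meeting the current international recommendation of 60 min of moderate to vigorous PA per day at 24-month follow-up". A bracket directly after this identifies the time point as T3, post-intervention 2, and refers to Fig. 1 (not available to this review).

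Under Evaluation, all variables are measured four times, T0 to T3:

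- T0 is baseline.
- T1 is "at the end of intervention 1, 4.5 months after baseline".
- T2 is "12 months after baseline, 7.5 months after the end of intervention 1".
- T3 is "post-intervention 2 (T3); end of intervention 2, 16.5 months after baseline".

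No assessment is listed after T3.

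Two other sections bear on the timing. Study design and population describes the experimental arm as one "which will receive a 24-month (6 weeks per year) multilevel, extended TPB-based program". The Overview under Design and implementation has the programme running from January to mid-April in each of two years. The analysis of mediators also takes physical activity at T3 as its dependent variable.

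**The concern.** The time point is part of the definition of a primary endpoint, and here one measurement carries two dates. A reader of the objective would expect a between-group difference two years after baseline. The schedule delivers one at 16.5 months, when the second round of the programme has just finished.

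If the objective's wording is carried into the report, an end-of-intervention result would be presented as a 24-month follow-up result. The distinction matters because the volitional phase is meant to build lasting activity habits. Whether an effect outlasts the second round is a different question from whether it exists when that round closes, and T3 can answer only the latter.

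**Working it through.** **1. Is the schedule consistent with itself?** Inputs are the dates in the Evaluation section.

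- T1 = 4.5 months, at the end of intervention 1.
- T2 − T1 = 12 − 4.5 = 7.5 months, which reproduces the stated gap between the end of intervention 1 and T2.
- T3 = 12 + 4.5 = 16.5 months, as stated, if year 2 repeats the spacing of year 1.

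Every stated interval reproduces.

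**2. Does the delivery calendar fit?** Inputs are January to mid-April (3.5 months) in two successive years, from the Overview.

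- From the start of round 1 to the end of round 2: 12 + 3.5 = 15.5 months.
- T3 at 16.5 months then implies a baseline about 16.5 − 15.5 = 1 month before the first January.
- Year 1 gives the same lead: 4.5 − 3.5 = 1 month.

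The calendar therefore supports 16.5 months.

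**3. How far off is the objective's label?**

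- 24 − 16.5 = 7.5 months.
- Time from the end of intervention 2 to T3, on the schedule's half-month scale: 0 months.
- A measurement truly at 24 months would fall 7.5 months after the second round, the same gap that T2 has after the first. It would be the year-2 counterpart of T2, and the schedule contains no such assessment.

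**4. Does the sample size depend on the label?** Inputs from the Power analysis: 35% at baseline, a 15-point difference, 80% power, two-sided 5%, mean cluster size 781, coefficient of variation 1.05, ICC 0.005, 15% loss.

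- Two proportions, 0.35 against 0.50: 170 per arm without continuity correction and 183 with it. The stated 180 is within 3% of the latter.
- Inflation factor: 1 + (781 × (1 + 1.05²) − 1) × 0.005 = 9.205.
- Total: 2 × 180 × 9.205 = 3314, or 2 × 183 × 9.205 = 3369. Both are within 3% of the stated 3400.
- Allowing for loss: 3400 / (1 − 0.15) = 4000, as stated.

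No term contains a follow-up time. Only the assumed 15% loss could depend on it.

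**The case against.** The strongest reply is that no analyst would be misled. The objective names T3, the Evaluation section dates T3, and the mediation analysis uses T3. The document also calls two annual rounds a 24-month programme, so the figure looks like shorthand for two programme years. It stands that the measurement intended as primary is identifiable and that nothing in the calculations changes. The label is still wrong, however: the objective gives 24 months as the follow-up time of the primary outcome, and that is what a reader would carry forward.

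Three stronger readings are tempting, and the document does not support them.

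- **The trial can say nothing about maintenance.** T2 is a randomised comparison of all variables 7.5 months after intervention 1, and the planned model includes time and its interaction with group. Persistence after year 1 can be estimated; persistence after the second round cannot.
- **The protocol claims 7.5 months of durability after the programme.** In its own labels, a 24-month programme is assessed at 24 months, so the two end together. The error is in time since baseline.
- **The primary endpoint counts activity supplied by the programme.** The questionnaire asks for activities "together with the frequency and duration of each activity over the last 7 days", and Table 1 schedules events as late as "M7 Sessions 7 & 8 (Week 6", so the recall period might overlap the final week in one arm. But the schedule gives dates only to the half-month, and a few days' delay after the last session would greatly reduce the overlap. Any estimate of its size needs assumptions about event length (Table 1 calls it variable), attendance, intensity and displaced usual activity. Two fully attended 60-minute events would average 120 / 7 = 17 min/day; two of 30 minutes, 9 min/day; two of 90 minutes, 26 min/day. Activity at these events is also part of what the intervention does, so measuring at its end is a legitimate choice.

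**Conclusion.** The concern holds for the time point. The protocol dates its primary endpoint at both 24 and 16.5 months, a discrepancy of 7.5 months. The internal arithmetic and the delivery calendar both support 16.5. Two consequences follow: no 24-month effect can be reported, and there is no measurement of persistence after the second intervention.

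This is more than a clerical matter, because it changes what the primary result may be said to show, but it does not undermine the design, the analysis model or the sample size. The conclusion rests on the Evaluation schedule being the operative one. Fig. 1 could not be checked, though it could not make both statements true.

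**What to change.** Reconcile Study objectives, Study design and population, and Evaluation:

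- State the primary endpoint as the proportion of children meeting the recommendation at T3, 16.5 months after baseline and at the end of the second intervention period, and delete the reference to a 24-month follow-up.
- Reconcile the 24-month description of the programme with the delivery calendar and with the date of T3.
- Limit the conclusion from T3 to an end-of-intervention effect, and name T2 as the evidence on persistence after year 1.

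The cost is wording in the protocol, and in any other trial document that repeats the label. The sample size stays at 4000. If a 24-month effect is really intended, an additional assessment is needed, with its own fieldwork and a fresh look at the 15% loss assumption.

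Stating the T3 assessment window relative to the last session would settle whether the 7-day recall overlaps the programme. Moving that window is optional: it would change what is being estimated and is not needed to correct this error.

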**Fig. 1 Fig1:**
[figure not shown]
Design of the Great Live and Move Challenge cluster randomized controlled trial. *Note*: The number of expected children in both groups has been estimated by a power calculation. Specific to cluster-randomized controlled trial design

The secondary objectives are to measure the effects of the GLMC on: *(i)* children’s scores for intentions, attitudes, subjective norms, perceived behavioral control, PA planning and level of perceptions of activity opportunities; and *(ii)* parents’ social support for their children’s PA and parental involvement in shared family PA.

### Study design and population

All the year 3 and year 4 children attending primary schools in the Hérault, Gard, and Aude departments of France (and their parents) are eligible to participate in the study. There is wide variation in the sociodemographic background and PA levels of children attending schools in these departments. The intervention involves children and their parents, and is implemented by multiple local, grass-roots partners, namely, school teachers, municipal officials and policy stakeholders from community agencies and district councils. To avoid contamination between the intervention and control groups randomization will be done at community of communes level (a community of communes is an administrative grouping of several cities or villages), thus all the schools in a given community of communes will represent a cluster.

The study is a two-armed prospective cluster-randomized, controlled intervention trial. Communities of communes will be randomized in equal proportions to one of the two study arms: 1) the GLMC experimental arm, which will receive a 24-month (6 weeks per year) multilevel, extended TPB-based program intended to promote PA; 2) the control arm, which will not receive any intervention (Fig. 1).

After randomization, schools belonging to the communities of communes and their teachers will be informed about the study and their arm allocation by a research assistant. A member of staff outside the research team will introduce data into the computer in separate datasheets so that the researchers can analyze data without having access to information about the allocation. Eligible children from schools and classes willing to participate in the study, and their parents, will receive a written note explaining the research goal, design, assessment protocol (including information about the wearing of accelerometers) and intervention content (see flow diagram of schedule in Fig. 2). Children with medical conditions or and children taking medication that would limit their physical activity will not be included. Children will be given consent forms to take home for their parents to sign. There are three independent consent forms providing: *(i)* consent to the child filling in questionnaires; *(ii)* consent to fill in the parental questionnaires; *(iii)* consent to the child wearing an accelerometer.

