##### Feasibility studies

Two preliminary pilot studies were conducted to confirm that it is feasible to deliver the GLMC intervention and evaluate the participating children and parents. These studies also represented an opportunity to assess the strengths and weaknesses of the intervention.

The first pilot study was carried out in and involved 306 children aged 7 to 11 years old attending 6 public schools and 104 of their parents. During this study we noted that children found the concept of ‘energy cubes’ very attractive; in fact they became something of a fad. We also found that the format of parents’ meetings (see Module 5, Table 1) were more attractive when they were held at the children’s schools rather than in town halls and organized as ‘round-table discussions about promoting PA’ with teachers, municipal officials and local policy stakeholders rather than organized as ‘PA promotion presentations’.

In 2015 a second study involving 793 children aged 7 to 11 years old from 16 public schools and 329 of their parents was carried out. This pilot study was used to test the feasibility of the evaluation procedure and the potential for recruitment. We found that it was feasible to administer the children’s questionnaires (evaluating self-reported PA, TPB variables and additional psychosocial variables) in a classroom setting (i.e.*,* 50–55 min for the completion of the questionnaire for a class of 20–25 children). We also confirmed the feasibility of the procedure for distributing and retrieving accelerometers from a subsample of children. The parents’ questionnaire was also reported to be feasible. Sixteen of the 53 schools (30%) that were contacted agreed to participate and the rates of return of signed consent forms were 86.7% for the child’s participation in the study, 37% for the wearing of an accelerometer by the child and 33.6% for completion of the parents’ questionnaire.

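### Schools and teachers learn their arm before schools agree, parents consent and, by inference, baseline is measured, so who joins may depend on the allocation

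*Protocol article*

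**What the plan says.** The order of events is in the protocol article, Study design and population. Communities of communes are randomised 1:1. After that, "schools belonging to the communities of communes and their teachers will be informed about the study and their arm allocation by a research assistant", so schools hear of the study and of their allocation in the same step. Next, "Eligible children from schools and classes willing to participate in the study, and their parents, will receive a written note", which covers the goal, design, assessments and intervention content. Then "Children will be given consent forms to take home for their parents to sign". One of the three forms is "consent to the child filling in questionnaires".

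The comparator is "the control arm, which will not receive any intervention". The Evaluation section sets four measurement points, the first being "pre-intervention 1 (T0); baseline". On uptake, Feasibility studies reports: "Sixteen of the 53 schools (30%) that were contacted agreed to participate". Signed forms for the child's participation came back for 86.7%.

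The only masking described is that someone outside the team enters data in separate sheets, so that analysts do not see the allocation.

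**The concern.** In a cluster trial, randomisation makes the communities comparable. It does not make the children comparable if they are recruited afterwards by people who already know the arm. Here schools, classes and families all decide after the school has been told.

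The two offers differ sharply. An intervention school takes on teacher training, 22 sessions and activity events. A control school takes on four rounds of assessment and receives nothing. Either package could attract or deter particular schools, and interest in physical activity is close to the primary outcome itself.

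T0 is exposed as well. The children's activity measure is self-reported and completed in the classroom. If the teacher already knows the arm, baseline reporting may be affected by it.

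What is at stake is whether the primary comparison at T3 can be read as the effect of the programme alone.

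**Working it through.** **1. Does disclosure precede enrolment and T0?**
- Study and arm are disclosed together, after randomisation. A school cannot have agreed to a study it had not yet heard of, so school agreement follows disclosure.
- The note and consent forms go to families in schools and classes already willing, so parental consent follows too.
- Consent covers the child's questionnaires, so T0 questionnaires cannot come before consent. T0 therefore follows disclosure. This last step is an inference from the order of the text and the consent requirement. The flow diagram (Fig. 2) is not shown, and no sentence says it outright.

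**2. How selective is participation?** (Feasibility studies, second pilot)
- Schools: 16/53 = 0.302, which reproduces the stated 30%. The exact 95% interval is 18% to 44%.
- Schools and children together, if the pilot rates carried over: 0.302 × 0.867 = 0.262. About 26% of eligible children would enrol, all after their school knew its arm.
- Neither rate is split by arm. They show that there is room for selection, not that selection differs between arms.

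**3. What do the planned safeguards cover?**
- Stratification by department and urban or rural setting (Randomization) balances the communities randomised, not the schools within them that agree.
- Intention-to-treat (Statistical analysis) applies to children once enrolled.
- Baseline comparison (Effectiveness analysis) describes those who joined. It cannot show how those who declined differed by arm.
- Age and sex, the covariates named in the same section, do not capture motivation.
- The longitudinal logit mixed model can be written, for group G and time T, as logit(p) = a + g·G + t·T + d·G·T + random effects, with d as the effect of interest. A constant difference between the arms' recruits enters g and leaves d alone. If recruits in one arm are readier to change, the difference in trend enters d. If knowing the arm shifts T0 reports in one arm by e on the logit scale and does not shift T3 reports, the change from T0 to T3 moves by −e, which also enters d.

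**4. Is there time to disclose later?**
- T1 is at the end of the first intervention, 4.5 months after T0 (Evaluation). Delivery lasts 3.5 months from January (Design and implementation). 4.5 − 3.5 = 1 month between T0 and the start of delivery.
- The first two months of delivery are preparation with local partners, so sessions for children start about 1 + 2 = 3 months after T0.
- Work to fit in at T0: about 160 classes (Power analysis) at 50 to 55 minutes each, so 160 × 50/60 = 133 to 160 × 55/60 = 147 class-hours, plus at least four days of accelerometer wear in 400 children.

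**The case against.** Several objections have force.

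- A reader might infer that the 30% uptake is itself arm-dependent. The document does not support that. It is one pooled pilot rate.
- A reader might assume that the bias favours the intervention because controls are offered nothing. Intervention schools also carry a six-hour teacher course and 22 sessions, most of them run by teachers. Which arm would draw the more motivated schools cannot be settled from the text.
- A reader might assume a selection gap of a few points and express it as a share of the 15-point target effect. No such gap is given, and the sum treats a difference in level as passing in full into the estimate. The time-by-group model takes out a stable gap on the logit scale.
- Families are not expressly told their arm; only schools and teachers are. Nothing says that the written note differs by arm.
- Enrolment numbers are already to be presented by randomisation group. Counts of those approached and declining may be in the full protocol.

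All of this stands and narrows the point. It does not change the stated sequence: schools decide knowing their arm, families decide after that, and nothing in the article conceals the allocation until they have agreed. This is a step the article fixes, not one it leaves out.

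**Conclusion.** The point holds as a design risk of unknown size and direction, and it should be fixed. Enrolment after disclosure is stated in the text. T0 after disclosure is a sound inference, subject to the flow diagram. With school uptake near 30% in the pilot, there is ample room for the arms to recruit differently.

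The planned model deals with a constant baseline difference. What remains is differential readiness to change, and baseline self-reports gathered in classrooms whose teachers know the allocation. Neither can be reliably repaired at analysis. The document does not show that bias will occur, and no percentage of the target effect can be attached to it.

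**What to change.** Leave randomisation where it is and move only the disclosure. Tell schools, teachers and families about the study, with the same note in both arms describing both conditions. Withhold the allocation until the school has agreed, consent forms are returned and T0 is complete. Then disclose the arm, before the January implementation step. Report the numbers of schools, classes and children approached, agreeing and consenting, by arm. If concealment proves impossible somewhere, that reporting matters all the more, together with adjustment for baseline.

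The cost is in the calendar. No sample size changes. Recruitment and T0 in about 160 classes must finish within or before the window of roughly one month, so recruitment has to start earlier. Teachers and local partners learn of their role at shorter notice before training and event planning begin.
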